#### Eliminated criteria

The enrolled patients will also be withdrawn for any of the following criteria: (1) poor adherence to medication with rates of less than 80% or more than 120%, (2) taking any drug prohibited in this program, and (3) discontinued the given drugs themselves. According to our previous study, the withdrawing rate will be not higher than 20%. All the records for all the eliminated patients will also be preserved.

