### Procedures and interventions

Patients in the experimental group will be treated with JHG for 52 weeks, while the control group are treated with a JHG placebo. JHG is a Chinese herbal compound medicine. The compounds of one dosage for JHG are found in Table 1. The placebo used in this study will contain 5% of the same components of JHG. All the JHG and placebo will be produced and packed by Jiang Yin Tian Jiang Pharmaceutical Co. Ltd., Jiangsu, People’s Republic of China, without any difference in the appearance, color, smell, and weight. The drug quality will be tested by the organization with specific qualifications before application and consistent with the required quality standards. Each dosage of JHG granules or placebo has been produced and packed into 4 bags with 10.9 g per bag (Batch number: 2006337). JHG or JHG placebo will be prescribed 2 bags each time, twice a day orally with 5 days on and 2 days off.

**Table 1 Tab1:** Components of Jin-shui Huan-xian granules

Chinese name	Latin name	Parts of the substances	Amount (g)
Ren Shen	*Radix Ginseng*	Root	6
Shu Di Huang	*Rehm,annia glutinosa Libosch*	Root tuber	12
Mai Dong	*Ophiopogon japonicus*	Root tuber	9
Gua Lou	*Trichosanthes kirilowii Maxim*	Mature fruit	9
Zhe Bei Mu	*Fritillaria thunbergii Miq*	Bulb	9
Mu Dan Pi	*Paeonia Suffruticosa Andrew*	Root bark	9
Zhi Yin Yang Huo	*Epimedium brevicornu Maxim*	Whole herb	6
Chao Bai Guo	*Ginkgo biloba L*	Mature seed	9
Chen Pi	*Citrus reticulata Blanco*	Peel of fruit	9
Zhi Gan Cao	*Glycyrrhiza uralensis Fisch*	Root and rhizome	9

At the same time, all the patients will also be treated with conventional modern medicine. Considering the side effects and costs, the application of pirfenidone and nintedanib will not be limited uniformly. During the whole procedure, all the patients will be visited every 13 weeks and receive given physical examinations. Blood and urine samples and exhaled breath condensate will be collected with the participants’ consent for further researches. If patients are under AE, the Chinese medicine granule or placebo will be suspended until the condition becomes stable. To improve the patients’ adherence, the remaining drugs and empty bags will also be returned except for regular telephone follow-up. The whole procedure for each patient is found in Fig. 2.

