#### Primary outcomes

##### Exacerbations of IPF

The frequencies of acute exacerbations of IPF, which is assessed by AEIPF-related hospitalization, is the primary outcome measure. AEIPF is characterized by significant respiratory deterioration, with an unknown cause within the past 1 month [28]. If the interval between any two AEIPF-related hospitalizations is less than 7 days, they are considered as one AE. The AE will be recorded at every visit, and the total number in the whole process (1-year treatment period) will be calculated. A higher number in a given period indicate the deterioration of IPF and a worse prognosis. A lower number in the experimental group will indicate better efficacy.

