##### Data management and statistical analysis plan

Statistical analysis will be conducted both in the intent-to-treat (ITT) and pre-protocol (PP) data. ITT analysis will be applied to analyze the safety data. All the data from any included patients will be analyzed regardless of their withdrawal from the trial. The PP analysis will be adopted to assess the efficacy of the interventions. If data permit, sub-group analysis will also be performed to help clarify the therapeutic effect of interventions.

All the *P* values will be set as two-tailed with a significant level of 0.05. Measurement data will be shown with mean ± SD, median, and inter-quartile range. Count data will be presented by frequency or composition ratio. Analysis of variance (ANOVA) will be used to test for the differences in continuous variables, with the chi-square test for categorical variables. If necessary, the paired *t*-test will be applied to intra-group comparison data with normal distribution and homogeneous variance, and the Wilcoxon signed-rank sum test will be used for non-normal distribution or uneven variance. Repeated-measures ANOVA will be used to test the continuous response variables that are measured at more than two time points for the same patient, such as 6MWT, clinical symptoms and signs, mMRC, and HRQoL. To improve the quality of data, all the data management and statistical analysis will be conducted by the Jiangsu Famous Medical Technology Co., Ltd. in Nanjing, China.

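### Study drug is suspended during an acute exacerbation, but the 80% adherence rule does not exempt that suspension, so a primary-outcome event can remove a patient from the efficacy set

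*Protocol article*

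**What the plan says.** Four statements in the protocol article bear on this point.

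- **Exacerbations of IPF.** The outcome is defined by "The frequencies of acute exacerbations of IPF, which is assessed by AEIPF-related hospitalization, is the primary outcome measure", and "the total number in the whole process (1-year treatment period) will be calculated".
- **Procedures and interventions.** "If patients are under AE, the Chinese medicine granule or placebo will be suspended until the condition becomes stable". No maximum length is given, and nothing says how suspended doses count towards adherence. Dosing is on 5 days of each week for 52 weeks, with visits every 13 weeks.
- **Eliminated criteria.** The rule on adherence is worded as follows: "The enrolled patients will also be withdrawn for any of the following criteria: (1) poor adherence to medication with rates of less than 80" (per cent). An upper limit of 120%, use of prohibited drugs, and patients who "discontinued the given drugs themselves" complete the list. Neither the denominator nor the time window of the adherence rate is defined. Records of eliminated patients are to be kept; whether their visits continue is not stated.
- **Data management and statistical analysis plan.** Both ITT and PP analyses are announced. ITT is then tied to the safety data, with a sentence that data are analysed whether or not the patient withdrew. Next comes "The PP analysis will be adopted to assess the efficacy of the interventions".

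**The concern.** Each rule is ordinary by itself, but together they form a chain. An exacerbation triggers suspension, suspension lowers the number of doses taken, an intake below 80% leads to elimination, and the set named for efficacy leaves out the eliminated. Membership of that set then depends on the outcome being compared. For exacerbations the article says that "A lower number in the experimental group will indicate better efficacy". If JHG does reduce exacerbations, the placebo arm loses more of its worst patients and the PP comparison understates the benefit. Patients removed in this way also drop out of the PP comparison of the other two primary outcomes, 6-minute walking distance and the progression-free proportion.

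A second consequence is conditional. If withdrawal ends data collection, later exacerbations, walking distance, lung function and deaths are lost for the patients who are doing worst. A later analysis plan cannot restore visits that did not take place.

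**Working it through.** The plan gives no figure for how many patients this affects, so there is none to reproduce. The check has three parts.

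**1. How much suspension breaches 80%?** Inputs from Procedures and interventions: 52 weeks, 5 dosing days per week, 13-week visits.

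- Dosing days: 52 × 5 = 260 over the trial; 13 × 5 = 65 per visit interval.
- Missed days that leave exactly 80%: 0.20 × 260 = 52 (10.4 weeks); 0.20 × 65 = 13 (2.6 weeks). The rule applies below 80%, so more than these must be missed.
- If intake on the other days is b, the share of time that can be suspended is 1 − 0.80/b.

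| Other intake b (assumed) | 1 − 0.80/b | Limit over 52 weeks | Limit per 13-week interval |
|---|---|---|---|
| 100% | 20.0% | 10.4 weeks (73 days) | 18 days |
| 95% | 15.8% | 8.2 weeks (57 days) | 14 days |
| 90% | 11.1% | 5.8 weeks (40 days) | 10 days |
| 85% | 5.9% | 3.1 weeks (21 days) | 5 days |

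**2. What does removing event patients do to a proportion?** Let p be the true risk of at least one exacerbation and q the share of those patients eliminated. If no other patients are removed, the risk seen in PP is p(1 − q)/(1 − pq). With assumed risks of 20% and 10%, a true difference of 10.0 points:

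- q = 25%: 15.8% versus 7.7%, difference 8.1 points.
- q = 50%: 0.10/0.90 = 11.1% versus 0.05/0.95 = 5.3%, difference 5.9 points.
- q = 75%: 5.9% versus 2.7%, difference 3.2 points.

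**3. What does it do to events per patient?** This is a simulation of 1,000,000 patients per arm. All of these inputs are assumptions: Poisson events with or without a gamma frailty of mean 1 and variance 1; other intake 95% (SD 6%, capped at 100%); exponential suspension per event, the same in both arms. Adherence = other intake × (1 − suspended weeks/52), and a patient is in PP if it is at least 80%. Nobody is lost to follow-up.

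| Rates per year | Frailty | Mean suspension | True difference | PP difference |
|---|---|---|---|---|
| 0.50 vs 0.35 | yes | 1 week | 0.15 | 0.14 |
| 0.50 vs 0.35 | yes | 2 weeks | 0.15 | 0.12 |
| 0.50 vs 0.35 | yes | 3 weeks | 0.15 | 0.10 |
| 0.50 vs 0.35 | yes | 4 weeks | 0.15 | 0.08 |
| 0.50 vs 0.35 | yes | 8 weeks | 0.15 | 0.05 |
| 0.50 vs 0.35 | no | 4 weeks | 0.15 | 0.11 |
| 0.15 vs 0.10 | either | 4 weeks | 0.05 | about 0.04 |

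In the 4-week case with frailty at the higher rates, 70% (placebo) and 74% (JHG) of patients with an exacerbation stay in PP, against 99% of those without. The rate ratio moves only from 0.70 to about 0.75.

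**The case against.** The strongest reply has four parts.

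- **The limit is high.** Over 52 weeks more than 10.4 weeks of suspension is needed with perfect intake otherwise, and exactly 52 missed days is 80% and no breach. This stands: removal is possible, not automatic. But the limit falls quickly with ordinary missed doses, and to about 18 days if adherence is judged per visit. The article does not fix the window.
- **The size rests on assumptions.** This also stands. The documents give neither an exacerbation rate nor a suspension length. The bias is small for short suspensions, without frailty or at low rates, and modest on the ratio scale.
- **An ITT analysis is promised.** It is, and data are to be analysed regardless of withdrawal. An ITT efficacy result may therefore exist. The set named for efficacy is still PP, and a promise to analyse data covers only data that were collected.
- **The article is condensed.** The adherence denominator could be defined in a full protocol or analysis plan. If suspended days were left out there, this route would close. The article as written, however, states an elimination rule without exemption and speaks of withdrawing patients, which concerns conduct as well as analysis.

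Three stronger readings are tempting, and the documents do not support them. First, a reader might infer that a patient on suspension is eliminated simply for being off drug. The third criterion concerns patients who stop by their own decision, so the firm route is the 80% rule. Second, a reader might infer that withdrawal ends follow-up and makes a valid ITT analysis impossible. Eliminated criteria does not say that visits stop. If adherence is judged over the full year, most breaches would be known only near week 52, when the outcomes have largely been collected. Third, a reader might infer that a patient who dies is eliminated for poor adherence. Nothing says so, and deaths are recorded and counted as an outcome.

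**Conclusion.** The point holds in this limited form. Under the rules as stated, a primary-outcome event can remove a patient from the set named for efficacy, because protocol-directed suspension is not exempt from the adherence limit. In every modelled case the bias runs towards no difference. At 0.50 versus 0.35 events per year with frailty it takes the difference from 0.15 to between 0.14 and 0.05 for mean suspensions of 1 to 8 weeks. Without frailty it is 0.11 at 4 weeks, and at the lower rates 0.05 becomes about 0.04. These sizes depend on assumed event rates, frailty, intake and suspension lengths equal in both arms; the existence of the mechanism does not. Harm to the ITT analysis is conditional on follow-up stopping at withdrawal, which the article leaves unclear and which these calculations do not quantify.

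**What to change.** Leave the suspension rule as it is; this point takes no position on it. Reconcile Eliminated criteria, Procedures and interventions, and the statistical analysis section as follows.

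1. Calculate adherence only over scheduled dosing days on which the patient was alive and not under a protocol-directed suspension, and state the window over which it is judged.
2. Make low adherence, prohibited drugs or self-discontinuation a reason to leave the PP set only, not the trial. Such patients keep the planned 13-weekly visits, with exacerbation and vital-status follow-up to week 52 unless they withdraw consent, so that all randomised patients can be analysed for efficacy.

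The cost is protocol wording and the remaining scheduled visits for a minority of patients. On the article's own upper limit of 20% for withdrawals, that is at most 0.20 × 312, or about 62 patients. The article reports 70 of 312 patients enrolled at submission, so at that point most of the follow-up could still be protected.

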### Sample size

The calculation formula (*n* = (*u*_*α*_ + *u*_*β*_)^2^(1 + 1/*k*)*σ*^2^/*δ*^2^) based on the comparison of the means of two independent samples has been adopted to calculate the target sample size. *N* and *k***n* represent the target sample size of the experimental and control groups, respectively. The total variance (*σ*^2^) will be represented by the sample variance (*s*^2^). The formulas *s*^2^ = (*s*_*e*_^2^ + *ks*_*c*_^2^)/(1 + *k*) and *δ* = |‾*x*_*e*_ − ‾*x*_*c*_| have also been adopted. ‾*x*_*e*_ and ‾*x*_*c*_ represent the means of the experimental and control groups, while *s*_*e*_ and *s*_*c*_ represent the standard deviation (SD), respectively. Two-tailed values of *α* and *β* are 0.05 and 0.01, respectively. The ratio of the experimental and control group samples in this trial is 1:1, so the *k* value is 1.

Based on our previous clinical trial (to be published), the frequencies of AEs and 6-min walking distance (6MWD) have been set up as the primary outcomes in this trial. There was a significant difference between the two groups in our previous study for AE. So, the calculation of sample size in this study will refer to 6MWD.

For 6MWD, the mean was 374.38 m in the experimental group and 342.57 m in the control group. The SD was 87.67 m in the experimental group and 81.18 in the control group. The target sample size in each group was 124. Taking a drop-out rate of 20%, the target sample size is 156 in each group, and the total target sample size is 312.

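### The stated type II error of 0.01 is not delivered: the protocol's own formula and inputs need 260 per group, and the planned 124 gives about 84% power

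*Protocol article*

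**What the plan says.** The Sample size section uses a formula "based on the comparison of the means of two independent samples has been adopted to calculate the target sample size", with n = (u_α + u_β)²(1 + 1/k)σ²/δ². The variance σ² is estimated by a weighted average of the two sample variances, and δ is the absolute difference in means. Allocation is 1:1, so k = 1.

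The error rates are given as: "Two-tailed values of *α* and *β* are 0.05 and 0.01, respectively".

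The planning values come from the sponsor's own earlier trial of 6MWD: "the mean was 374.38 m in the experimental group and 342.57 m in the control group", and "The SD was 87.67 m in the experimental group and 81.18 in the control group".

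The result is: "The target sample size in each group was 124. Taking a drop-out rate of 20%, the target sample size is 156 in each group", which makes 312 in total.

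The Data management and statistical analysis plan section confirms the sidedness: "All the *P* values will be set as two-tailed with a significant level of 0.05". The article gives no other beta and no power figure. The 99% used below is simply 1 minus the stated beta.

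**The concern.** The planned difference is about 0.38 of a standard deviation (31.81/84.49). A type II error of 1% for an effect of that size calls for far more than 124 patients per group, so the result looked too small for its stated inputs.

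This calculation is the only justification given for 312 patients, because 6MWD is the only outcome used for sizing. If beta is misstated, sponsor, ethics committee and readers are told that the planned 6MWD effect would be missed about one time in a hundred. At 124 evaluable per group the true figure is nearer one in six.

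**Working it through.** **Inputs** (all from the Sample size section; two-sided alpha also from the analysis section)

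- δ = 374.38 − 342.57 = 31.81 m
- s² = (87.67² + 81.18²)/2 = 7138.11, so s = 84.49 m
- k = 1, so (1 + 1/k) = 2
- 2s²/δ² = 14276.2/1011.9 = 14.11
- Two-sided alpha 0.05: u_α = 1.960
- Beta 0.01: u_β = 2.326

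**Attempt to reproduce 124**

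n = (1.960 + 2.326)² × 14.11 = 259.2, so 260 per group. The stated figure is less than half of this and is not reproduced.

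**Could a different reading of the inputs give 124?**

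| Alpha 0.05 | Beta | n per group |
|---|---|---|
| two-sided | 0.20 | 111 |
| two-sided | 0.15 | 127 |
| two-sided | 0.10 | 149 |
| two-sided | 0.05 | 184 |
| two-sided | 0.01 (as stated) | 260 |
| two-sided | 0.005 (beta literally halved) | 291 |
| one-sided | 0.10 | 121 |
| one-sided | 0.01 | 223 |

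Swapping the two error rates (alpha 0.01, beta 0.05) gives 252 two-sided or 223 one-sided. Omitting the factor (1 + 1/k) at the stated error rates gives 129.6, so 130. No variant gives 124. The two closest, 127 and 121, each depart from what is written: the first needs beta 0.15, and the second needs beta 0.10 together with a one-sided alpha.

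**What 124 per group delivers**

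- Standardised difference: 31.81/(84.49 × √(2/124)) = 2.965
- Power at two-sided 0.05: Φ(2.965 − 1.960) = Φ(1.005) = 0.842, so beta is about 0.16. The noncentral t gives 0.840.
- With all 156 per group analysed: power 0.914, so beta is about 0.09 (noncentral t 0.912).
- Difference detectable with 99% power at 124 per group: (1.960 + 2.326) × 84.49 × √(2/124) = 46.0 m, against the planned 31.81 m.

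**What beta 0.01 would need**

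260 evaluable per group; 260/0.8 = 325 randomised per group, 650 in total.

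**Dropout step**

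124/0.8 = 155 against 156 stated. This step is sound; the error lies before it.

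**The case against.** The arithmetic is not in dispute. The case on the other side is about weight and framing.

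- **The design survives.** Power of 84% at the full 20% loss, or 91% with none, is acceptable on the protocol's own assumptions. Beta serves only to set the sample size; correcting it changes no test, estimate or decision rule. This stands: the trial is not shown to be underpowered, and nothing in the article says a null 6MWD result would be interpreted through planned power.
- **It may be a misprint for 0.10.** One-sided alpha with beta 0.10 gives 121, and 124 per group gives 90.7% power at one-sided 0.05. This does not rescue the text. It still misses 124, it contradicts two-sided testing in both sections, and at two-sided alpha beta 0.10 needs 149. It does mean that an intention to have 99% power is not established.
- **The 16% miss rate is the upper end of a range.** The Eliminated criteria section expects withdrawal of no more than 20%, so beta runs from about 0.09 to 0.16. This is fair. However, efficacy is assessed on the per-protocol set, so losses count, and even the favourable end is about nine times the stated value.
- **The words two-tailed probably belong to alpha only.** This is a reasonable reading of a loosely worded sentence. A two-tailed beta is not a defined input for a superiority test and should go, but the finding does not rest on it.
- **The analysis planned for 6MWD is repeated-measures ANOVA.** The 84% therefore describes the simple comparison of two means on which the protocol sized the trial, and should be labelled so.

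**Conclusion.** The point holds. The stated error rates and the stated sample size cannot both be right: the printed formula and inputs require 260 per group, not 124. On the protocol's own means and SDs, with two-sided alpha 0.05, the design has 84.2% power with 124 evaluable per group and 91.4% with 156. The stated beta of 0.01 is not reached under any loss rate, including none, and no single misprint reconciles the section.

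These figures assume the protocol's planning values are correct, a two-sample comparison of mean 6MWD, and 6MWD tested alone at 0.05. Any multiplicity allowance for the other primary outcomes is a separate matter. The document does not show how 124 was obtained. This is a false statement of the type II error in the sole justification for the sample size; it does not show that 312 patients are too few.

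**What to change.** Keep 312 patients. The sponsor should state which alpha, sidedness and beta actually produced 124, remove the beta of 0.01 and any reference to a two-tailed beta, and replace the sentence with one the inputs support, for example:

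> With a two-sided alpha of 0.05, 124 evaluable patients per group give about 84% power (beta about 0.16) to detect a difference of 31.81 m in 6MWD, assuming a pooled SD of 84.5 m and a comparison of two independent means. Power is 91% if all 156 per group are analysed.

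The wording should remain two-sided, to agree with the analysis section.

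The cost is one corrected sentence and a less favourable stated power, with no extra patients and no change to the analysis. The Trial status section reports 70 patients enrolled with recruitment continuing at submission, so as of that report the correction can be made before results are known.

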### Ethics, oversight, recruitment, and dissemination

The study has been approved by the Ethical Committees of the First Affiliated Hospital of Henan University of Traditional Chinese Medicine with an identifier (version 2019.07.18.1.0.1.0) 2019HL064-01. Any other revisions of the study protocol will also be submitted to the ethical committee for approval. The whole process of the trial will also be supervised by the Ethical Research Committees of the First Affiliated Hospital of Henan University of Traditional Chinese Medicine. The ethics committee is composed of people with different professions, including non-medical people. The approved protocol will protect the interests of participants. The informed consent will be obtained from all individual participants by the special screener in every research center. Any adverse event will also be submitted to the ethical committees as soon as possible. All the participants will provide written informed consent. Blood and urine samples and exhaled breath condensate will be collected with the participants’ consent for further researches. The authors are accountable for the accuracy of all aspects of the study. Any question related to any part of the work will be investigated and resolved.

Open recruitment for IPF patients will be performed both in outpatient and inpatient. Publishing recruitment advertisements will also be adopted, and the enrolled patients will be observed in 11 research centers in China, which are the First Affiliated Hospital of Henan University of Traditional Chinese Medicine, Shanghai Shuguang Hospital, Dongzhimen Hospital of Beijing University of Traditional Chinese Medicine, the Second Affiliated Hospital of Tianjin University of Traditional Chinese Medicine, Hebei Province Traditional Chinese Medicine Hospital, Qingdao Hici Hospital, Henan Provincial People’s Hospital, Henan Province Hospital of Traditional Chinese Medicine, Third Affiliated Hospital of Henan University of Traditional Chinese Medicine, Zhengzhou Chinese Medicine Hospital, and Zhengzhou First People’s Hospital. All the sub-centers have the qualification and experience in performing TCM trials. Recruitment will last for 12 months from September 2020 or until the target sample is completed. The results of this study will be disseminated to the public in peer-reviewed journals without any patient’s personal information. The raw data will also be available upon request to the authors.

